### Inclusion and exclusion criteria

Inclusion criteria: All patients of 18 years and older visiting the ED, with a temperature of ≥ 38.2 °C (100.8 °F) are eligible. Temperature is measured using an ear thermometer, in triage. Eligible patients need to provide written informed consent.

Exclusion criteria: Patients with specific immunocompromised status, defined as neutropenia with absolute neutrophil count less than 0.5×10^9^/L, current chemotherapy, or post-organ transplantation are excluded. Furthermore, pregnant patients, moribund patients and patients with a diagnosis that requires primary surgical intervention, or within 72 h after surgery are excluded. Patients are randomized using a minimization procedure [20]. The factors for minimization are imbalance in randomization result and study site. The randomization result is allocated at patient enrolment by a computer generated algorithm.

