### Sample size calculation and statistical analyses

Sample size and power analysis: For the three primary objectives the following analyses are used: a) a superiority analysis for the reduction in the percentage of febrile patients receiving antibiotics. b) a noninferiority analysis for safety, and c) an analysis of the test characteristics (sensitivity and specificity) of the biomarker PCT and CRP. The total sample size calculation is based on a power analysis for each of these three primary outcome measures; the total sample size is the maximum of the required sample sizes for the different primary outcome measures.For the superiority analysis of the reduction in the prescription of antibiotics, we assumed that antibiotics are initially prescribed at the ED to 73 % of the patients in the control arm, and that the intervention will reduce this percentage to 53 %, based on a careful estimate using recent literature [14]. To obtain 80 % power to detect a significant difference between the two groups using a two-sided Fisher’s exact test with a significance level of 5 %, the required sample size is 101 patients per group.The noninferiority analysis for the safety objective uses a composite endpoint consisting of ICU admittance, 30-days mortality or second ED visit within 14 days. For an accurate sample size calculation, we first analyzed ED data from the Erasmus MC from January 2011 until May 2012. In this data set, the prevalence of the composite safety endpoint was 12.7 % (102 cases out of 809 patients). We used this percentage as the expected rate in the control group. Using a noninferiority margin of 7.5 %, a noninferiority analysis comparing the rates in the control and the intervention groups requires 244 patients in each group to obtain 80 % power with a one-sided alpha of 5 %. To account for 10 % expected dropout, the total sample size must be 550 patients.The third sample size calculation is based on a comparison of sensitivity and specificity of PCT and CRP in patients with infection. We used data from a meta-analysis [21, 22] to estimate the accuracy of PCT and CRP for bacterial infection. We conservatively assumed zero correlation between the test results of PCT and CRP for the diagnosis of bacterial infection. For the prevalence of bacterial infections, we used data from our pilot study [3] to obtain a representative estimate of the prevalence of bacterial infections, which led to an estimated prevalence of 68 %. Based on the results of the meta-analysis, the sensitivity of PCT was 0.83 and for CRP 0.73; the specificity was 0.88 for PCT and 0.60 for CRP. Using McNemar’s test, 340 patients with a bacterial infection (340/0.68 = 500 patients in total) are required to obtain 80 % power for detecting a difference in sensitivity between PCT and CRP. Forty-one patients without a bacterial infection (41/(1–0.68) = 129 patients in total) are required to obtain 80 % power for detecting a difference in specificity between PCT and CRP. To ensure sufficient power for all three primary outcome measures, we thus use a sample size of 275 patients per group (550 patients in total).

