
Statistical analyses for the primary study parameters:Antibiotics use. The percentage of patients that are prescribed antibiotics is compared between the PCT-guided group and control group using a Fisher’s exact test. Demographic parameters (age, sex, mortality), medical parameters (medication use, comorbidity, temperature, CRP and PCT measurements), hospital admission related parameters (hospital admittance, hospital length of stay, ICU admittance, ICU length of stay) are compared between the PCT-guided group and control group using Fisher’s exact tests for dichotomous variables, chi-square tests for categorical variables with more than two categories, t-tests for continuous variables that are normally distributed, and Kruskal-Wallis tests for continuous variables that are not normally distributed. A logistic regression analysis will be used to determine the influence of these parameters on the proportion of antibiotics prescriptions in the control group and the PCT-guided therapy group. To select the independent variables in this logistic regression model, we will use a stepwise backward approach in which only the independent variables are retained that have a significant effect using a significance level of 5 %; however, the variable group (PCT-guided group versus control group) will be included in the model irrespective of the results. In the event of missing values in possible confounding data, like intoxications and prescription drugs use, we will use multiple imputation. Both an intention to treat analysis and a per protocol analysis will be performed. Physician adherence to the PCT guidance will be determined.Safety. Significant differences between the PCT-guided group and control group in the composite safety endpoint are determined using a one-sided upper 95 % confidence limit for the difference in proportion between the PCT-guided group and the control group. This confidence interval will be calculated using the method of Agresti and Caffo [23]. Noninferiority of the intervention will be established if the 95 % confidence interval excludes 7.5 %, i.e. if PCT-guided prescription of antibiotics does not increase the rate of the composite endpoint by more than 7.5 percentage points. Differences in hospital length of stay will be assessed using the Kruskal-Wallis test.Accuracy of PCT and CRP. In all patients, the final diagnosis of the etiology of fever will be determined. Also, it will be determined if there is a bacterial infection. The variables “confirmed bacterial infection” and “suspected bacterial infection” will serve as gold standards for the evaluation of the accuracy of the biomarkers CRP and PCT. These will be determined retrospectively, using culture results and all diagnostic tests available. In all patients, both PCT and CRP levels will be available for statistical analysis. The ability to predict bacterial infection of both PCT and CRP will be evaluated using receiver operating characteristic curves, and the area under the curve will be calculated. In addition, logistic regression will be performed to analyze the effects of PCT and CRP levels on the probability of a bacterial infection. The independent variables in this analysis are age, sex, PCT, CRP, temperature, comorbidity, and other variables that have a *p* < 0.1 for the difference between groups. We will account for possible non-linear effects of age, PCT, CRP and temperature by using appropriate transformations of these variables.

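### Extra covariates in the supplementary bacterial-infection regression are picked by a p < 0.1 screen between undefined groups, with no limit to variables known at ED presentation

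*Protocol article*

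**What the plan says.** The accuracy part of the section Sample size calculation and statistical analyses (Protocol article) adds a model to the ROC analysis: "logistic regression will be performed to analyze the effects of PCT and CRP levels on the probability of a bacterial infection". Its covariates are given as "The independent variables in this analysis are age, sex, PCT, CRP, temperature, comorbidity, and other variables that have a" p-value "< 0.1 for the difference between groups". So six variables are forced in and any others enter through a 10 % screen. For this model the article does not say which groups are compared, names no candidates, and sets no limit on when a candidate must be known.

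In the rest of that section the word group refers to the trial arms. In the antibiotic regression, "the variable group (PCT-guided group versus control group) will be included in the model irrespective of the results". The descriptive comparisons use the same sense: "hospital admission related parameters (hospital admittance, hospital length of stay, ICU admittance, ICU length of stay) are compared between the PCT-guided group and control group". On allocation, the section Inclusion and exclusion criteria states: "Patients are randomized using a minimization procedure".

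Two statements under Outcome measures also matter. The accuracy outcome is defined by sensitivity, specificity and AUC. The experts who adjudicate suspected bacterial infection may use the clinical course.

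**The concern.** This is a stated selection rule, not a detail left to a fuller document. It can be read in two ways, which give different models, and each reading has its own weakness.

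Under the arm reading, a variable is chosen because it differs between randomised groups. Whether a variable confounds PCT or CRP with infection is a different question, and the screen does not address it.

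Under the infection reading, a variable is chosen because it is associated with the outcome. Admission, ICU stay, length of stay and mortality may well be associated with infection because they follow from it. Adjusting for them would remove part of the signal that the model is meant to describe. It would also put elements of the clinical course on the predictor side, when that course helps to define suspected infection.

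At stake are the adjusted PCT and CRP effects reported under the accuracy objective.

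**Working it through.** The protocol gives no power or sample-size figure for this regression, so there is no stated figure to reproduce. The checks below take from the protocol the size ("we thus use a sample size of 275 patients per group (550 patients in total"), the assumed infection prevalence of 68 %, and the assumed antibiotic rates of 73 % and 53 %. All other effect sizes are assumptions.

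**1. Possible candidates.** The only list of compared parameters stands in the antibiotics part and has 12 items. Six are already forced into the infection model (age, sex, PCT, CRP, temperature, comorbidity). That leaves medication use, mortality, hospital admission, hospital stay, ICU admission and ICU stay. Five of these six are not known at ED presentation. The article does not say that this list is the candidate pool, nor does it rule the list out.

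**2. Arm reading, baseline variables.** With k independent variables that differ between arms only by chance, the expected number entering is 0.1k and P(at least one) = 1 − 0.9^k:
- k = 5: 1 − 0.590 = 41 %
- k = 10: 1 − 0.349 = 65 %
- k = 20: 1 − 0.122 = 88 %

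A real confounder is also balanced apart from chance, so it too enters only about 10 % of the time.

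**3. Arm reading, variables the intervention changes.** Take antibiotic prescription as an example, should it count as a candidate. At the protocol's own rates, the standard error of the difference is √[(0.73 × 0.27 + 0.53 × 0.47)/275] = √(0.4462/275) = 0.0403, so z = 0.20/0.0403 = 4.97 against a threshold of 1.645. It would pass almost surely.

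**4. Simulation of both readings.** There were 1,000 data sets of 550 patients.
- Confounder C: standard normal and not among the six named variables. The log odds of infection Y are 0.85 + 0.6C, which gives a prevalence of about 0.68.
- PCT = 1.3Y + e, with e standard normal.
- CRP = 0.8Y + 0.3C + 0.4e + 0.9 × (standard normal noise).
- Six pure-noise baseline variables.
- Length of stay = 0.8Y + 0.3 PCT + noise. Log odds of admission = −1 + 1.2Y + 0.4 PCT.
- Log odds of antibiotics = −0.5 + 1.5Y, plus 1.2(PCT − 0.9) − 0.5 in the PCT arm.

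Screening was by t-test at p < 0.1. Mean log odds ratios (odds ratios in brackets):

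| Extra covariates | PCT | CRP |
|---|---|---|
| None | 1.11 (3.05) | 0.51 (1.66) |
| True confounder, pre-specified | 1.18 (3.25) | 0.35 (1.42) |
| Arm screen, baseline candidates | 1.12 (3.07) | 0.49 (1.63) |
| Arm screen, plus stay and admission | 1.09 (2.97) | 0.49 (1.63) |
| Arm screen, plus antibiotics as well | 0.97 (2.65) | 0.49 (1.64) |
| Infection screen, baseline candidates | 1.18 (3.26) | 0.35 (1.42) |
| Infection screen, plus stay and admission | 0.83 (2.29) | 0.36 (1.43) |
| Infection screen, plus antibiotics as well | 0.68 (1.97) | 0.36 (1.43) |

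The arm screen kept the true confounder in 12 % of data sets. With stay and admission in the infection screen, the PCT log odds ratio falls by 1 − 0.828/1.180 = 30 %.

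**5. Second simulation, other assumptions.** There were 600 data sets of 495 patients (550 less 10 % dropout), 68 % infected, with PCT shifted by 1 SD and CRP by 0.8 SD. Admission and stay depended on infection and PCT. Both passed the infection screen in every data set. The PCT log odds ratio fell from 1.012 to 0.827, that is 1 − 0.827/1.012 = 18 % (odds ratio per SD 2.75 to 2.29).

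**The case against.** The strongest reply is that the damaging variables are not in the text. Admission, ICU stay, length of stay and mortality are listed for the antibiotic comparison, while the accuracy paragraph speaks only of other variables. A condensed article may leave the candidate list to the full protocol. This stands: a reader might infer that the plan directs consequences of infection into the model, but the article only fails to exclude them. The 18 to 30 % is therefore conditional on their being screened in.

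A reader might also infer that chance imbalance distorts the marker effects. The simulation does not bear that out: the arm screen on baseline candidates gives 1.12 and 0.49, practically the same as no extra covariates (1.11 and 0.51). The 65 % for at least one null variable describes an irrelevant rule, not a bias.

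Nor can it be said that every reading is worse than the six named variables alone. An infection screen confined to baseline candidates recovered the target, whereas a model without the confounder did not. The fixed list alone would omit an unlisted confounder every time. The remedy therefore has to leave room for further pre-specified confounders.

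Finally, the model is an addition to the ROC analysis. It is meant to describe marker effects, not to supply an ED prediction rule. PCT and CRP are forced in, and about 550 × 0.32 = 176 uninfected patients are expected, so a few extra terms are unlikely to cause serious overfitting. Over-optimistic p-values after screening are possible in principle, but they were not quantified and are not relied on here.

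The reply does not rescue the rule itself. On the section's own use of the word group, the screen is irrelevant to confounding. On the other reading, it has no safeguard against post-ED variables.

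**Conclusion.** The point holds for the supplementary regression only, at low to moderate severity. The selection rule is ambiguous. Read as arms, it picks variables on grounds unrelated to confounding and missed a real confounder in about 88 % of simulated trials. Read as infection status, it lets in variables arising after the ED visit. If they enter, the PCT log odds ratio falls by roughly 18 to 30 %, a range that rests wholly on assumed effect sizes and assumed candidates. Even then the PCT odds ratio was 2.29 in both simulations, still a clear association.

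A reader might take this as a threat to the primary accuracy result or to the trial's main comparisons. The document does not support that: sensitivity, specificity, AUC, the Fisher test on antibiotic prescription and the noninferiority analysis do not depend on this model.

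**What to change.** Replace the p < 0.1 clause with a covariate set fixed before analysis: the six variables already named, with the planned non-linear terms, plus any further confounders chosen in advance on subject knowledge. State that every covariate must be known at ED presentation, and that admission, ICU stay, length of stay, mortality and other post-ED variables are excluded.

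The change affects only the analysis wording, and the article describes recruitment as still open. The small cost is that a baseline predictor nobody foresaw is left to a sensitivity analysis.

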
## Statistical analyses for the secondary study parameters

The study will involve an economic evaluation from the societal perspective comparing PCT-guided therapy with usual care. The economic evaluation will use the technique of cost-minimization analysis, which compares two interventions of identical effectiveness to find out which is less costly. Total treatment costs will be compared between the PCT-guided therapy arm and the control arm, including costs for PCT testing (intervention group only), other diagnostic tests, ED visits, antibiotics and other medications, adverse effects of antibiotics, hospital admissions, return visits to the general practitioner (GP) and other related medical consumption. These costs will be taken into account during the one-month follow-up period. Unit prices will be calculated using real economic cost prices or using standard cost-prices for health economic evaluations [24].

Unit prices will be multiplied by the quantities for each resource used, and then summed over the separate types of resource to give a total cost per patient. In addition, differences in labor productivity losses will be evaluated by comparing costs of absence from work (absenteeism) and reduced productivity while at work (presenteeism). Moreover, productivity losses related to unpaid work (e.g., household work, shopping, odd jobs, and voluntary work) will be included. Productivity losses will be evaluated using the Productivity Costs Questionnaire [25]. Mean total costs will be calculated for patients in each treatment group.

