Estimated yearly costs associated with antibiotic resistance in Europe are in the range of 1.5 billion euros, comprising extra healthcare costs and productivity losses caused by infections due to antibiotic-resistant bacteria [17]. PCT-guided therapy may contribute to a reduction of these enormous costs. It may lead to a reduction in costs of antibiotics and additional diagnostics tests, such as blood cultures in non-bacterial disease. Costs of hospital admissions could be reduced as admission for observation may become obsolete. As an added effect, there may be a reduction of productivity losses, related to paid and unpaid work. Patients may be able to return to their daily activities faster.

The current evidence on the cost-effectiveness of PCT-guided therapy consists of retrospective hypothetical models. One study analyzed the cost-effectiveness of PCT testing in patients hospitalized for community-acquired pneumonia with a mathematical model [18]. The authors showed that a PCT-guided protocol would cost less and would be more effective than usual care [18]. Recently, a model-based study from the US assessed the economic impact of PCT testing in patients with acute respiratory tract infections. The authors documented that PCT-guided care was cost saving in inpatient, ICU and outpatient settings, mainly due to a reduction in antibiotic costs. Total yearly savings at the US national level were calculated at 1.6 billion dollars [19].

These estimates only included costs of PCT testing and savings on costs of hospitalization, excluding savings from other care consumption and productivity losses, which cannot be estimated at this stage. There is a need to broaden the evidence base to promote the efficient use of PCT-guided therapy in patients with fever presenting at EDs.

The primary objectives of this study are to determine a) the efficacy and b) the safety of PCT-guided therapy, and c) the accuracy of the biomarker PCT for bacterial infections. The secondary objective is to study the cost-effectiveness of PCT-guided therapy.

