### Outcome measures

#### Primary outcome measures

The efficacy of PCT-guided therapy is defined as the percentage of patients who are prescribed antibiotics in the ED.The safety outcome measure consists of a composite endpoint of 30 days mortality, intensive care unit (ICU) admission within 30 days, or a return visit to the ED within 14 days.The accuracy of the definitive diagnosis is reported for PCT and CRP using the sensitivity, specificity, and the AUC of the diagnosis of bacterial infections. The definitive diagnosis is defined in two ways. 1. As “confirmed bacterial infection”, in which culture – and PCR results that fit the clinical case presentation are used to report presence of bacterial infections. 2. As “suspected bacterial infection”, in which two independent physicians will give their expert opinion on the presence of a bacterial infection using culture results, image modalities and clinical course, in case of discrepancy, a third physician will decide.

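### The cost-effectiveness objective is pursued only by cost-minimization, whose premise of identical effectiveness contradicts the efficacy hypothesis and cannot be shown by the noninferiority test

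*Protocol article*

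**What the plan says.** The Background of the protocol article states: "The secondary objective is to study the cost-effectiveness of PCT-guided therapy". The Abstract says the same. The section Statistical analyses for the secondary study parameters gives the method: "The economic evaluation will use the technique of cost-minimization analysis, which compares two interventions of identical effectiveness to find out which is less costly". It lists the cost items (PCT testing, other diagnostics, ED visits, antibiotics and other drugs, adverse effects of antibiotics, admissions, GP visits, other related care) over one month and adds productivity losses. It says total costs are compared between arms and ends with the summary measure: "Mean total costs will be calculated for patients in each treatment group". No effect measure enters the economic analysis.

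On effects, Primary outcome measures states: "The efficacy of PCT-guided therapy is defined as the percentage of patients who are prescribed antibiotics in the ED". Sample size calculation and statistical analyses plans "a superiority analysis for the reduction in the percentage of febrile patients receiving antibiotics". Its starting assumption is that "antibiotics are initially prescribed at the ED to 73 % of the patients in the control arm"; under PCT guidance a rate of 53 % is expected. Safety is a composite of 30-day mortality, ICU admission within 30 days and ED return within 14 days. It is judged by whether a one-sided upper 95 % Agresti-Caffo limit for the difference lies below 7.5 percentage points.

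**The concern.** Comparing costs alone answers a value-for-money question only when the outcomes can be taken as equal, and the article's own definition of the method says so. Here the two outcomes that the article calls efficacy and safety are handled in ways that do not fit that premise. On efficacy, success of the primary hypothesis makes the premise false. On safety, success rules out only a large excess.

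At stake is how the economic result can be read. If PCT-guided care is cheaper but has somewhat more composite events, or costs slightly more but avoids many prescriptions, a cost comparison alone does not show the trade-off. The Background says that studies of this kind serve those who set priorities under limited budgets, and the trade-off is what such readers need.

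**Working it through.** **Inputs**, all from Sample size calculation and statistical analyses: antibiotic rates 73 % and 53 %, two-sided 5 %, 80 % power, 101 per group; composite rate 12.7 % in both arms, margin 7.5 points, one-sided 5 %, 80 % power, 244 per group; 10 % dropout, 275 per group (550 in total).

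**1. The plan's own figures reproduce.**
- Noninferiority: n = (1.645 + 0.842)² × 2 × 0.127 × 0.873 / 0.075² = 243.7, so 244 per group, as stated. Dropout: 488 / 0.9 = 542.2, so 543 against the stated 550.
- Superiority: the two-proportion formula gives 91 per group, and 101 with continuity correction. This matches the article: "with a significance level of 5 %, the required sample size is 101 patients per group".

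**2. Efficacy.** The planned difference is 73 − 53 = 20 points. On the measure that the article names as efficacy, the arms are expected to differ, and 275 per group is well above the 101 needed to show it.

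**3. Safety: what still passes.** The Agresti-Caffo upper limit is d + 1.645 × √[p₁(1−p₁)/(n+2) + p₂(1−p₂)/(n+2)], with pᵢ = (xᵢ+1)/(n+2) and d = p₁ − p₂. The control count is set near 12.7 %.

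| n per group | Events, PCT vs control | Observed excess | Upper limit | Noninferior? |
|---|---|---|---|---|
| 244 | 36 vs 31 | 2.05 points | 7.18 | yes |
| 244 | 37 vs 31 | 2.46 points | 7.62 | no |
| 275 | 42 vs 35 | 2.55 points | 7.41 | yes |
| 275 | 43 vs 35 | 2.91 points | 7.80 | no |

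For the first row, p₁ = 37/246 = 0.1504, p₂ = 32/246 = 0.1301, d = 0.0203 and the standard error is 0.0313. The limit is 0.0203 + 1.645 × 0.0313 = 0.0718.

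Exact binomial enumeration shows that if PCT-guided care truly added 3 points, noninferiority would still be declared 41.8 % of the time at 244 per group and 44.9 % at 275.

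**4. Safety: could the trial show equivalence?** This requires both one-sided 95 % limits to lie within ±7.5 points when both arms truly have 12.7 %. The normal approximation to the power is 2Φ(0.075/SE − 1.645) − 1, with SE = √(2 × 0.127 × 0.873 / n).
- n = 244: SE = 0.03015 and 0.075/SE = 2.488, so the power is 2Φ(0.843) − 1 = 0.60.
- n = 275: SE = 0.02840 and 0.075/SE = 2.641, so the power is 2Φ(0.996) − 1 = 0.68.

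Exact enumeration gives 0.603 and 0.681.

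**5. What the costs capture.** By the article's list, an avoided prescription lowers drug and adverse-effect costs, and a return visit or ICU stay raises visit and admission costs. The list has no item for the health loss itself, most plainly a death. It also has nothing for benefits of lower prescribing after one month, such as less resistance, which the Background gives as a main reason for the trial.

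**The case against.** The best defence is that antibiotic prescribing is a process measure and a form of resource use, so it belongs on the cost side. Identical effectiveness would then refer to patient outcomes, for which the Discussion cites a systematic review that found no difference in mortality or treatment failure. Secondary outcome measures also lists only cost items under cost-effectiveness, so the cost question as posed can be answered.

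Part of this stands. The efficacy limb is the weaker one for that reason, and safety is the stronger. But the article itself labels prescribing as efficacy, uses the cited review to justify the margin rather than the economic method, and nowhere names the outcome on which the arms are taken as equal.

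Four stronger readings are tempting and are not supported:
- *That avoided prescriptions and safety events count for nothing.* They enter through their costs.
- *That the cheaper arm would be declared preferable whatever its safety.* The article states no such rule, and safety is a separate primary outcome with its own criterion.
- *That a passing trial means one extra event per 13 patients.* That is 1/0.075, the margin that the confidence limit must stay below. The largest observed excess that passes is about one per 49 (1/0.0205) to one per 39 (1/0.0255).
- *That the article is at fault for not describing bootstrap intervals or acceptability curves.* A journal article may leave such detail to a fuller plan. The same holds for any condition on when cost-minimization applies.

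**Conclusion.** The point holds as a conflict between a stated method and the trial's own hypotheses, not as missing detail. The premise of identical effectiveness is contradicted on efficacy by a planned 20-point difference. On safety it is not established: an observed excess of about 2 to 2.5 points still passes, and with truly equal arms equivalence within 7.5 points would be shown only about 60 to 68 % of the time. These figures assume a control rate of 12.7 % and 244 to 275 evaluable patients per group. The equivalence figure uses two one-sided 5 % limits, which the plan does not itself propose.

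A reader might infer that the economic evaluation is worthless. It is not: the cost comparison is valid as a cost comparison. What it cannot do alone is support a cost-effectiveness conclusion when outcomes differ or equality is unproven. The objective is secondary, and the sample size and primary analyses are unaffected.

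**What to change.** Plan a cost-effectiveness analysis on the data already collected. Report the mean cost difference between arms alongside the differences in the composite safety endpoint and in antibiotic prescribing, with uncertainty assessed jointly for cost and effect. Incremental cost per composite event avoided and per prescription avoided are possible summaries. Keep cost-minimization at most as a supplementary analysis that names the outcome on which the arms are taken as equal and applies only if the trial results support that equality.

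The cost is some extra health-economic analysis, with no new patients or data. There are two drawbacks. The ratios have no agreed willingness-to-pay value, and they count some resource use (prescriptions, ICU stays, ED visits) in both cost and effect. The differences themselves should therefore be shown first, with the ratios as a secondary display.
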